## Abstract

**Abstracts:**

## Background

Allergic reaction is a hypersensitive response caused by immunoglobulin E (IgE)-dependent mast cell activation. In response to IgE receptor cross-linking or other stimuli, mast cells initiate exocytosis of the contents of secretory granules. These include vasoactive amines, arachidonic acid metabolites, chemokines, and cytokines [1,2]. These pro-inflammatory mediators are responsible for activating mast cells in allergic inflammation and the hypersensitive response [3-6]. Therefore, an agent or agents capable of attenuating the production of these mediators may be used as anti-inflammatory/anti-allergic agents. Since the notion that a daily intake of certain food having anti-allergic activity has the potential to reduce or eliminate the need for drugs is generally accepted, the anti-inflammatory/anti-allergic activities of the chungkookjang (CKJ) have been screened for this purpose [7].

Soybean-based fermented foods, such as CKJ is a Korean traditional food. It is prepared by fermenting unsalted soybeans with *Bacillus subtilis *for several days. It has a long history of popular use by the Korean people and is sometimes used for topically for inflammatory skin disorders. Several isoflavonoids such as genistein and daidzein have been identified among the bioactive compounds in the CKJ [8]. During the fermentation period, the content of the flavonoid aglycones increases because of hydrolysis of the flavonoid glycosides [9]. The CKJ is also containing the poly-gamma-glutamic acid (gamma-PGA). Gamma-PGA is an anionic polymer that is composed of D- and L-glutamic acid units connected by gamma-amide linkages between alpha-amino and gamma-carboxylic acid groups [10]. Gamma-PGA is mainly produced by *Bacillus subtilis *during fermentation processes of soybeans and not present in humans [11]. Gamma-PGA is water soluble, biodegradable, edible and non-toxic properties, raising interest in a broad range of industries including food and cosmetics [12]. Furthermore, recent reports have indicated anti-allergic activity and immune modulatory activities of gamma-PGA [7,13-16].

Histamine is one of the important mediators that elicit a variety of symptoms such as wheal and flare response. Since these histamine-related symptoms provoke the urge to scratch, often impairing the quality of life, measures to suppress and control these symptoms are required. In the development of a new anti-histamine, the histamine-induced wheal and flare skin test has been used most frequently. The histamine-induced wheal and flare test is based on the measurement of local swelling caused by plasma extravasation (wheal) and reflex vasodilatation (flare) after histamine challenge [17]. Therefore, the histamine skin prick test may be useful for assessing aspects of drug activity during the early clinical development of a new anti-histamine.

The aim of this study is to evaluate the efficacy and safety of the CKJ, a dietary supplement for the treatment of allergic skin symptoms. This study will be first pilot study about the improvement of skin hypersensitivity reaction of the CKJ in healthy volunteers. The results of this study will give us the clinical of biochemical parameters such as IgE, histamine, and cytokines between the placebo and CKJ groups. On the basis of the results, we will suggest the optimal design, precise sample size, and primary outcome for a further large scale RCT.

## Methods/design

### Study objectives

The objectives of this RCT are to study whether the CKJ pills can alleviate the histamine-induced wheal and flare skin responses in healthy subjects.

#### Primary objective

To evaluate the efficacy of the CKJ pills on histamine-induced wheal and flare skin responses in healthy subjects after 12 weeks of consumption.

#### Secondary objectives

To evaluate the following factors in healthy subjects after 12 weeks of consumption on:

A) Change of IgE and histamine concentrations

B) Change of cytokines such as IFN-gamma, IL-4, IL-10, and TNF-alpha

C) Change of eosinophil cationic protein

### Ethics

The study protocol and the written informed consent were approved by the Functional Foods Institutional Review Board of Chonbuk National University Hospital (CUH IRB 2010-02-007). Each participant will be notified regarding the study protocol. Written informed consent will be obtained from each participant.

### Study/trial design

This study is a randomized, double-blind, placebo-controlled, two-armed parallel clinical trial, comparing the CKJ pills to placebo pills. The design of the study will integrate rigorous in accord with principles set out in the Declaration of Helsinki and the Good Clinical Practice guidelines. Our study plan is summarized in Figure 1.

**Figure 1 F1:**
[figure not shown]
**Flow diagram for study**. Summary of the study flow.

### Inclusion criteria for participation in the trial

#### Inclusion criteria

Participants will be included if they meet the following criteria:

A) Healthy volunteers aged 20 to 80 years

B) Positive response to histamine skin prick test(a wheal size > 3 mm)

C) Ability to give informed consent

#### Exclusion criteria

Participants will be excluded if they:

A) have severe generalized skin conditions such as eczema, psoriasis, and atopy(hay fever, asthma)

B) have severe allergic reactions in the past

C) have taken oral anti-histamines or topical corticosteroids in the preceding 3 months

D) have any acute or chronic illness

E) have cardiovascular disease, liver or kidney disease

F) have allergies on soybean foods

G) have taken any prescribed or investigation medication during the 8 weeks preceding enrolment.

H) have history of drug or alcohol abuse in prior 2 months

### Recruitment

60 participants will be recruited through local advertising and doctor referrals from hospital outpatients and general practice clinics. Interested participants can telephone or email the trial coordinators at the trial conducting sites for further information. Participant information and consent forms will be sent to interested individuals to read over prior to scheduling their first visit.

### Randomization

After enrollment, participants will be randomly assigned to one of the two groups, either the CKJ pills group or placebo pills group. The allocation ratio will be 1:1 in blocks of 2. Randomization will be performed at a site remote from trial location. Random numbers will be generated by a computerized random-number generator through the block-randomization method of a software program (Excel, Microsoft Office 2007) for sequence generation. At the time of randomization participants will draw an envelope. Each envelope contains a number that is concealed to the treatment allocation. Randomization sequence and allocation will be concealed to all study subjects, research staff, investigators and pharmacists until completion of the study. The allocation list will be protected by password access files and held by a non-investigator independent. In the event of an emergency medical situation the individual's randomization code and group allocation can be identify.

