#### Sample size

Sample size calculation is performed; primary outcome measure will be the histamine-induced wheal size, whereby 5.0 square millimeters is assumed a clinically relevant difference between the two groups, with a standard deviation of 6.85, alpha set on 5% and power on 80%. This resulted in a required number of 24 subjects in each group. Assuming a dropout rate of 20%, a total of 60 subjects will be enrolled in this trial.

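### Fixed blocks of 2, stated in the protocol, mean that one emergency code break can also disclose the block partner's arm; varying blocks of 4 and 6 weaken this leak at almost no cost

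*Protocol article*

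**What the plan says.** The Study/trial design section describes a double-blind trial with two parallel arms. The Randomization section then fixes the block: "The allocation ratio will be 1:1 in blocks of 2". It gives no reason for this size and does not mention varying it.

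The same section sets the safeguards. The sequence is generated at a remote site, and a person independent of the investigators holds the password-protected list. On envelopes it says: "Each envelope contains a number that is concealed to the treatment allocation". On concealment it says: "Randomization sequence and allocation will be concealed to all study subjects, research staff, investigators and pharmacists until completion of the study".

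It also provides for opening a single code: "In the event of an emergency medical situation the individual's randomization code and group allocation can be identify". It does not say that the block size is withheld from staff, and the protocol itself prints it. Nor does it say how the numbers in the envelopes map to positions on the list.

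**The concern.** Two is the smallest block that a 1:1 ratio allows, and it gives the least protection once any allocation is known. The section promises that allocation stays concealed until the study ends, yet it allows codes to be opened one at a time. With blocks of 2, opening one code discloses two allocations to anyone who knows the pairing, so the break cannot stay individual.

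The stake is the primary outcome. Under Primary outcome, the wheal and flare are read 15 minutes after the prick, as a mean diameter or by planimetry, and an observer's expectation can influence such a reading. In Table 1 the histamine prick test appears at screening and at Week 12 only. A partner whose arm is disclosed during treatment may therefore still have the single post-randomization reading to come.

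**Working it through.** **1. The plan's own figure.** The Sample size section gives a difference of 5.0 square mm, SD 6.85, alpha 5% and power 80%, and arrives at 24 per group. The normal formula is n = 2 × (z_alpha + z_power)² × SD² / difference².

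- One-sided 5%: 2 × (1.645 + 0.842)² × 46.92 / 25 = 23.2, so 24 per group. With 20% dropout, 24 / 0.8 = 30 per group, 60 in total. The stated figures reproduce.
- Two-sided 5%: 2 × (1.960 + 0.842)² × 46.92 / 25 = 29.5, so 30 per group before dropout.

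The article does not state the sidedness. That is a separate matter, so both versions are carried below. Block size does not enter this calculation.

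**2. What one known allocation reveals.** In a 1:1 block of size k, one known member leaves k − 1 others, of whom k/2 are in the opposite arm. The probability that a given block-mate is in the opposite arm is (k/2) / (k − 1):

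- k = 2: 1/1 = 1.00
- k = 4: 2/3 = 0.67
- k = 6: 3/5 = 0.60

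The values for 4 and 6 assume that the observer knows who shares the block. If the sizes vary and are withheld, they are upper limits after one code break.

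**3. A suspected allocation.** If a suspicion about one participant is right with probability p, then in a block of 2 the inference about the partner is also right with probability p. Certainty arises only at p = 1, that is, after a disclosure.

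**4. Predictability if every earlier allocation were known.** With blocks of 2, the first place is a coin toss and the second is certain: (0.5 + 1) / 2 = 75% correct, with 30 of 60 allocations determined by the one before. Guessing the under-represented arm in 5,000 simulated sequences of 60 gives 71% for blocks of 4, 68% for blocks of 6 and 69% for a random mix of 4 and 6. If no earlier allocation is known, accuracy is 50% for any block size.

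**5. Cost of blocks of 4 and 6.** Sixty is a multiple of 2, so blocks of 2 end at exactly 30:30. With random 4s and 6s the last block may be cut at participant 60. All sizes are even, so the cut falls after 2 of 4, 2 of 6 or 4 of 6, and in each case the arms differ by at most 2. The worst split is 31:29, which occurred in about 23% of simulated sequences. Power by the normal approximation:

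| Split | One-sided | Two-sided |
|---|---|---|
| 30:30 | 0.8814 | 0.8070 |
| 31:29 | 0.8811 | 0.8066 |
| 24:24 (after 20% dropout) | 0.8116 | 0.7152 |
| 25:23 | 0.8110 | 0.7144 |

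The largest loss is 0.7152 − 0.7144 = 0.0008, or 0.08 percentage point.

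**The case against.** The strongest reply is that the safeguards already described do most of the work. The trial is double-blind, the envelopes hold only a number, an independent person holds the list, and assignment follows enrolment. Emergency code breaks in healthy volunteers taking a food-based pill may be few. Each one exposes at most one further person. The primary outcome is touched only if the disclosure reaches the assessor before the partner's Week 12 test and the assessor knows who the partner is. All of this stands. It limits how often the leak would matter, but it does not stop a disclosed allocation from fixing its partner's.

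A reader might infer more than the article supports, in four ways:

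- **That half of the allocations can be predicted at enrolment.** The 30 of 60 and the 75% against 69% hold only if all past allocations are known, which the blinding and concealment are meant to prevent.
- **That a guess from taste, smell or tolerability unblinds two people.** A guess gives no certainty about either, and the article reports no such difference between CKJ and placebo pills.
- **That the draw destroys the sequence, because "At the time of randomization participants will draw an envelope".** The sentence does not say that the choice is free, and order of issue is a detail that a condensed article may leave to the full protocol. A free draw would also make the partner harder to identify, so this reading competes with the present point and does not add to it.
- **That larger blocks leave a noticeably uneven trial.** An imbalance of 3 can occur part-way through a sequence of 4s and 6s, but at n = 60 it is at most 2.

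**Conclusion.** The point holds in a limited form. With 1:1 blocks of 2 stated in the protocol, disclosure of one allocation gives the block partner's arm with probability 1.00, against at most 0.67 or 0.60 for a given block-mate in a block of 4 or 6. This works against the concealment that the same section promises.

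The conclusion rests on two assumptions: that participant numbers follow list order, or that the pairing can otherwise be worked out, and that at least one allocation becomes known during the trial. The article describes no scrambling that would defeat the first. It gives no figure for the second, so neither the expected number of exposed participants nor a bias in the wheal result can be calculated. This is an avoidable weakness with a very cheap remedy. It is not evidence that the allocation is predictable as the trial is planned.

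**What to change.** Before enrolment, have the independent list holder generate the sequence in randomly ordered blocks of 4 and 6. Replace the sentence on blocks of 2 with a statement that block sizes vary and are withheld from site staff, and keep the sizes in a document that only the list holder can see. The emergency provision needs no change on this account.

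The cost is one new list and one amended sentence. The sample size stays at 60, the final split is at worst 31:29, and power falls by less than 0.1 percentage point. If an exact 30:30 is wanted, six blocks of 4 and six of 6 in random order give 24 + 36 = 60 with no cut block. Larger blocks weaken the leak but do not remove it: two disclosed members of the same arm in one block of 4 would still fix the other two.

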### Outcome measures

#### Primary outcome

The primary outcome is the difference on wheal and flare skin responses induced by histamine challenge at baseline and three months after randomization. The histamine-induced wheal and flare skin test will be performed by histamine challenge via epicutaneous prick. The resulting wheal is a sign of the direct vascular effects of histamine, namely increased vascular permeability and skin blood flow, while the flare reflects vasodilatation due to histamine-induced reflex neuropeptide release from local nerve terminals. The wheal and flare response will be assessed 15 min after the test and will be assessed as the mean diameter or by planimetry.

#### Secondary outcomes

Secondary outcomes will be shown by the mean change of IgE, histamine, eosinophil cationic protein, IFN-gamma, IL-4, IL-10, and TNF-alpha. These biomarkers will be checked at weeks 0 (baseline) and 12 (end of the trial). The schedule of assessments is presented in Table 1.

**Table 1 T1:** A brief study schedule at every visit

	*Screening Visit 1*	*Baseline Visit 2*	*Visit 3*	*Visit 4*	*Visit 5*	*Follow up (Visit 6)*
	
	*D-21 ~D-1*	*Week 0 D0*	*Week 4 D28*	*Week 8 D56*	*Week 12 D84*	*Week 16 D112*
***Informed consent form***	◯					

***Demographic information taking***^***1***^	◯					

***Medical history taking***	◯					

***Inclusion/exclusion criteria check***	◯	◯				

***Physician examination***^***2***^	◯				◯	

***Drinking/smoking taking status***^***3***^	◯				◯	

***Vital sign measurement***	◯	◯	◯	◯	◯	

***Concomitant drugs check***	◯	◯	◯	◯	◯	

***Electrocardiogram(ECG)***	◯				◯	

***Histamine skin prick test***	◯				◯	

***Laboratory test***^***4***^	◯				◯	

***Histamine & ECP***		◯			◯	

***Study product distribution***		◯	◯	◯		

***Compliance checking***			◯	◯	◯	

***Adverse event monitoring***			◯	◯	◯	◯

***Diet, physical exercise counseling***^***5***^		◯	◯	◯		

◯ *: Item need to be performed during the visit*

^1 ^*Sex, date of birth, age, contact address and phone number*

^2 ^*Include present illness, past history taking*

^3,5 ^*Risk factors such as alcohol drinking, smoking, severe exercise and other dietary supplement intake will be managed*

^4 ^*Blood test(WBC, RBC, hemoglobin, hematocrit, platelets count, AST, ALT, ALP, gamma-GTP, albumin, BUN, creatinine, glucose, total bilirubin, total protein, total-cholesterol, triglyceride, LDL-C, HDL-C, IgE), urine test(specific gravity, pH, Protein, Ketone, Glucose, bilirubin, urobilinogen, nitrite, microscopic (RBC, WBC))*

### Statistical analysis

#### Baseline data and Outcomes data

Statistical analysis will be performed using SAS version 9.0 for Windows (SAS Institute, Cary, NC, USA). Data will be presented as mean±SD values. The Chi-square test will be performed to determine differences at baseline in frequencies of categorized variables between the groups. A linear mixed-effects model will be applied to repeated-measures data for each continuous outcome variable. Fixed effects will be included treatment group, treatment visit, and interaction between treatment group and visit. When the analysis of variance indicated significant differences among groups, *post hoc *test (Turkey's test) will be used to separate the differences between groups before and after the 12-week intervention period. A value of p < 0.05 will be considered statistically significant.

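### The mixed model treats the pre-treatment value as an outcome and does not adjust for it: valid and unbiased, but less precise than a baseline-adjusted week-12 comparison from the same data

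*Protocol article*

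**What the plan says.** Under Statistical analysis, Baseline data and Outcomes data, the protocol article states: "A linear mixed-effects model will be applied to repeated-measures data for each continuous outcome variable". It then lists the model terms: "Fixed effects will be included treatment group, treatment visit, and interaction between treatment group and visit". No baseline covariate is named. If the analysis of variance is significant, Tukey comparisons "will be used to separate the differences between groups before and after the 12-week intervention period".

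The primary outcome is defined on two occasions: "The primary outcome is the difference on wheal and flare skin responses induced by histamine challenge at baseline and three months after randomization". Table 1 marks the histamine prick test at the screening visit and at week 12 only. Everyone has a pre-treatment wheal, because eligibility requires one: "Positive response to histamine skin prick test(a wheal size > 3 mm" or, in effect, any larger reading. The Secondary outcomes section summarises the biomarkers as mean changes and gives weeks 0 and 12 as the measurement times.

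The Sample size section takes wheal size as primary: "5.0 square millimeters is assumed a clinically relevant difference between the two groups". Its other inputs are an SD of 6.85, a 5% alpha and 80% power. This gives 24 per group, and 60 enrolled after 20% dropout.

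**The concern.** With one value before treatment and one at week 12, the wheal is repeated-measures data only if the pre-treatment value is one of the two outcome rows. The wording about comparing groups before and after the intervention fits that reading. Such a model offers two treatment contrasts.

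- **Group-by-visit interaction.** With complete data this equals the difference between groups in mean change. It subtracts the whole baseline value, which over-corrects whenever ρ is below 1.
- **Group difference at week 12.** With complete data this makes no use of the baseline.

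A week-12 comparison with the pre-treatment value as a covariate weights the baseline by what it predicts. It therefore extracts more from measurements that are already scheduled. It also removes the effect of chance baseline imbalance, which is not negligible in groups of this size. What is at stake is precision, in a trial whose stated group size leaves little margin.

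**Working it through.** **Inputs.** From the Sample size section: difference 5.0 mm², SD 6.85, 24 per group, alpha 5%, power 80%, dropout 20%. Not in the document: ρ (assumed range 0.3 to 0.9), the sidedness of alpha, and whether 6.85 is the SD of the week-12 value or of the change.

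**The plan's own figure.** n per group = 2(SD/Δ)²(z_α + z_β)².
- One-sided 5%: 2(6.85/5)²(1.645 + 0.842)² = 23.2, so 24. This matches.
- Two-sided 5%: 2(6.85/5)²(1.960 + 0.842)² = 29.5, so 30. This does not match.
- Enrolment: 48/0.8 = 60. This matches.

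The stated 24 therefore reproduces only as a one-sided calculation. The planned F test and Tukey comparisons at p < 0.05 are two-sided. A two-sided t-test with SD 6.85 and 24 per group has 69.7% power.

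**Variances.** With equal SD σ at both times and n per group, the variance of each contrast is (2/n) times:
- interaction (change): 2σ²(1−ρ)
- week 12 only: σ²
- baseline-adjusted: σ²(1−ρ²)

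The ratio of interaction to adjusted is 2(1−ρ)/(1−ρ²) = 2/(1+ρ). The ratio of week-12-only to adjusted is 1/(1−ρ²).

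| ρ | 2/(1+ρ) | 1/(1−ρ²) |
|---|---|---|
| 0.3 | 1.54 | 1.10 |
| 0.5 | 1.33 | 1.33 |
| 0.7 | 1.18 | 1.96 |
| 0.8 | 1.11 | 2.78 |
| 0.9 | 1.05 | 5.26 |

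Estimating the covariate costs one degree of freedom (45 instead of 46) and raises the adjusted variance by about 2%. With that cost, adjustment still beats the interaction up to ρ of about 0.96 (2/1.022 − 1). It beats the week-12-only contrast from ρ of about 0.15 (1 − ρ² < 1/1.022).

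**Power, case A: 6.85 is the SD of the week-12 value.** Two-sided 5%, 24 per group, t-based, with the covariate cost included in the adjusted column.

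| ρ | SD of change, 6.85√(2(1−ρ)) | Interaction | Week 12 only | Adjusted SD, 6.85√(1−ρ²) | Adjusted |
|---|---|---|---|---|---|
| 0.3 | 8.10 | 55% | 70% | 6.53 | 73% |
| 0.5 | 6.85 | 70% | 70% | 5.93 | 81% |
| 0.7 | 5.31 | 89% | 70% | 4.89 | 93% |
| 0.8 | 4.33 | 97.5% | 70% | 4.11 | 98% |

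**Power, case B: 6.85 is the SD of the change.** The adjusted SD is 6.85√((1+ρ)/2).

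| ρ | Interaction | Adjusted SD | Adjusted |
|---|---|---|---|
| 0.3 | 70% | 5.52 | 86% |
| 0.5 | 70% | 5.93 | 81% |
| 0.7 | 70% | 6.32 | 76% |
| 0.8 | 70% | 6.50 | 73% |
| 0.9 | 70% | 6.68 | 71% |

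Simulation at ρ = 0.5 (SD 6.85, 24 per group) gave standard errors of 1.96 (change), 1.99 (week 12 only) and 1.73 (adjusted).

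**Chance imbalance.** In case A the baseline mean difference has a standard error of 6.85√(2/24) = 1.98 mm². At ρ = 0.5, an imbalance of that size moves the change contrast by (1−0.5) × 1.98 = 0.99 mm² one way and the week-12-only contrast by 0.5 × 1.98 = 0.99 mm² the other way. The adjusted contrast removes it on average.

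**The case against.** The strongest reply is that nothing here is an error. A group, visit and interaction model is a standard, valid analysis of a randomised trial. It also agrees with the primary outcome as a difference between two times and with the secondary outcomes, introduced by "Secondary outcomes will be shown by the mean change of IgE, histamine, eosinophil cationic protein". That is correct: the mean-change wording is consistent with the model and is not a second fault. The reply might add that a condensed article leaves covariates to the full protocol or SAP, and that the trial calls itself a pilot. The first part carries less weight here, because the article does list the fixed effects. The second lowers the urgency but does not make the less precise contrast preferable.

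Several stronger readings are tempting, and the document does not support them.

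- **That the baseline information is wholly lost.** This holds only for the week-12 contrast. A change score uses the baseline in part, and the protocol does not say which contrast is primary.
- **That the trial is underpowered under this model.** This depends on ρ and on which SD 6.85 is. In case A the interaction reaches roughly 80% at ρ of about 0.6, and 89% at 0.7.
- **That adjustment restores all the power missing from a two-sided test.** It does not at ρ = 0.3 in case A (73%), nor at ρ of 0.7 to 0.9 in case B (76% down to 71%).
- **That the planned estimate is biased.** Randomisation protects it. Imbalance adds noise, not systematic error.

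**Conclusion.** The concern holds as one of efficiency. The planned contrasts are valid, but across the range of ρ shown each is less precise than a week-12 comparison adjusted for the pre-treatment value. The loss is substantial at low to moderate ρ: at 0.5 both contrasts have 1.33 times the adjusted variance, and power is 70% against about 81%. At high ρ the loss against the interaction is small: 97.5% against 98% at 0.8 in case A, and 70% against 71% at 0.9 in case B. The week-12-only contrast does progressively worse as ρ rises. Adjustment may therefore recover some or all of any power shortfall, depending on ρ.

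These figures assume 24 completers per group, a two-sided 5% test, equal SDs at the two times, complete data and approximate normality. That the pre-treatment value is a level of visit is inferred from the two-occasion schedule and the before-and-after wording. No other reading makes the wheal repeated-measures data.

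**What to change.** Name as the primary contrast the week-12 CKJ-minus-placebo difference in wheal, adjusted for the participant's pre-treatment wheal, and report it with its 95% CI. Do the same for each biomarker. Two specifications serve.

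- **ANCOVA:** the week-12 value on treatment group and the pre-treatment value. Using the change as the response with the same covariate gives the identical treatment estimate, so the mean-change presentation can stay.
- **Mixed model with the baseline mean constrained equal between groups** and an unstructured covariance for the two times. This agrees with ANCOVA when data are complete. It also keeps participants who lack a baseline or a week-12 value, whom ANCOVA drops.

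The choice should be fixed before unblinding. The Sample size section should also say whether 6.85 is the SD of the week-12 value or of the change, and whether alpha is one- or two-sided. The cost is one line of model specification and one degree of freedom; no new measurements or participants are needed.

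### The only stated decision rule, an unspecified ANOVA followed by Tukey's test, does not say which test decides efficacy, and under its repeated-measures readings it costs much of the power

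*Protocol article*

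**What the plan says.** The section Baseline data and Outcomes data (Protocol article, Statistical analysis) applies a linear mixed model to each continuous outcome, with fixed effects for treatment group, visit and group by visit. One decision rule follows. "When the analysis of variance indicated significant differences among groups", Tukey's test (printed as Turkey's) "will be used to separate the differences between groups before and after the 12-week intervention period". The significance threshold is p < 0.05, and sidedness is not given.

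The trial has two parallel arms (Study/trial design). The primary outcome concerns the wheal and flare response at baseline and at three months (Primary outcome). Table 1 places the skin prick test at screening and at week 12 only.

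The Sample size section plans for one simple comparison, "whereby 5.0 square millimeters is assumed a clinically relevant difference between the two groups", "with a standard deviation of 6.85", alpha 5% and power 80%. It concludes: "This resulted in a required number of 24 subjects in each group".

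**The concern.** With two arms there is one between-arm comparison, so a global test followed by a multiple-comparison procedure has nothing to sort out. With two measurement times, the group-by-visit interaction is exactly the difference between arms in change from baseline. It is in the model, but the plan does not say that it decides anything.

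The rule refers instead to an ANOVA showing differences among groups. Taken at its word, that is the group main effect. This term averages the baseline visit, where randomisation makes the expected difference zero, with week 12, so an effect of 5.0 mm² is tested as 2.5 mm². If Tukey's test then covers the four group-by-visit means, the week-12 comparison carries a penalty for six pairwise comparisons and makes no use of each participant's own baseline.

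At stake is whether a trial sized for a 5.0 mm² difference has a fair chance of detecting it, and whether two analysts following the text would run the same primary test.

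**Working it through.** **Inputs from the Protocol article.** Effect 5.0 mm², SD 6.85 mm², alpha 5%, power 80%, 24 per arm, 20% dropout, 60 in total (Sample size); two arms (Study/trial design); two measurement times (Table 1).

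**Assumptions.** SD 6.85 is the SD at a single visit (the article does not say whether it is of a value or of a change). Tests are two-sided at 5%. The baseline to week-12 correlation ρ is not given and is varied over 0.3, 0.5 and 0.7.

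**1. The plan's own figure.** n per arm = 2[(z_α + z_β)·SD/δ]².
- One-sided 5%: 2 × (2.486 × 6.85/5)² = 23.2, so 24.
- Two-sided 5%: 2 × (2.802 × 6.85/5)² = 29.5, so 30 (31 by the exact t calculation).
- Dropout: 24/0.8 = 30 per arm, 60 in total.

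The stated 24 is therefore reproduced with a one-sided 5% alpha. At two-sided 5%, 24 per arm gives about 70% power by the t-test. That 70% is the reference for judging the decision rule.

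**2. What each candidate test measures** (24 per arm, ρ = 0.5, SD² = 46.92, critical t on 46 df = 2.01).
- Group main effect: expected difference 5.0/2 = 2.5; SE = √(46.92 × (1 + ρ)/2 × 2/24) = 1.71; ratio 1.46.
- Interaction (difference in change): expected difference 5.0; SE = √(46.92 × 2(1 − ρ) × 2/24) = 1.98; ratio 2.53.
- Week-12 difference alone: expected difference 5.0; SE = √(46.92 × 2/24) = 1.98; ratio 2.53.
- Baseline-adjusted week-12 difference, approximately: SE = √(46.92 × (1 − ρ²) × 2/24) = 1.71; ratio 5.0/1.71 = 2.92.

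Tukey's test over four means with 46 df has critical value 3.77/√2 = 2.67, against 2.01 for a single comparison.

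**3. Power by reading of the rule** (simulation, 20,000 trials per setting, true effect 5.0 mm² at week 12 only).

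| Reading, 24 per arm | ρ = 0.3 | ρ = 0.5 | ρ = 0.7 |
|---|---|---|---|
| Group main effect alone | 33% | 30% | 27% |
| Group main effect, then four-mean Tukey at week 12 | 29% | 28% | 26% |
| Interaction, then four-mean Tukey at week 12 | 35% | 39% | 44% |
| Two-group test at week 12 (Tukey equals the t-test) | 70% | 70% | 70% |
| Interaction alone | 55% | 70% | 89% |
| Baseline-adjusted week-12 difference | 72% | 81% | 93% |

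The two Tukey rows move by about a point between runs and with the error variance used: a separate run gave 26–28% and 34–43%.

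With all 30 per arm retained, the main-effect gate plus Tukey gives 37/34/32%, the interaction gate plus Tukey 48/52/57%, the interaction alone 66/79/95% and the baseline-adjusted difference 83/89/97%.

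**4. False positives.** With no treatment effect at 24 per arm, the two-step readings declare a week-12 difference in 0.7–1.0% (main-effect gate) or 0.2–0.4% (interaction gate) of trials. In these readings the cost is lost power, not an inflated error rate.

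**The case against.** The strongest reply is that the text is loose rather than wrong. A reader might infer that the plan does not test the treatment effect at all. The article does not support that: the interaction is fitted, the p < 0.05 threshold is stated generally, and a Tukey comparison of the arms at week 12 is itself a between-arm comparison. Nor does the article say that Tukey's test covers all four group-by-visit means. It could mean the two arms compared at each time, and if the ANOVA is a two-group test at week 12, nothing is lost. These points stand, and they are why the result is given as a range over readings. The two-group reading does, however, fit poorly with a repeated-measures model and with a post hoc step described as covering both before and after the intervention.

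A reader might also infer that efficacy would be claimed from a before/after change that is significant in one arm only. The sentence speaks of differences between groups, and no such claim is planned. Any false-positive rate for it would need a common drift and a decision rule that the protocol does not state. Regression to the mean after screening on wheal size is expected equally in both arms and does not bias the between-arm contrast.

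Finally, the article calls the study a pilot, and full detail may sit in an analysis plan. But the article sizes the study formally for 80% power, and it states a rule rather than leaving one open. The concern is with the stated rule.

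**Conclusion.** The point holds as a badly fixed decision rule. The plan does not say which F test decides, attaches no decision to the interaction that measures the difference in change, and adds a Tukey step that two arms do not need. At 24 per arm, power is about 26–28% with the group main effect as gate plus four-mean Tukey, about 34–43% with the interaction as gate plus that Tukey step, and about 70% if the ANOVA is a two-group test at week 12. The interaction alone gives 55–89% and the baseline-adjusted difference 72–93%.

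These figures rest on the assumed correlation of 0.3 to 0.7, on 6.85 being a single-visit SD and on two-sided testing. If 6.85 were the SD of the change, the interaction alone would have the same SE as the week-12 comparison above (1.98), hence about 70% power whatever the correlation.

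It would be wrong to charge the whole gap from 80% to this rule. The step from 80% to about 70% arises because 24 per arm corresponds to a one-sided 5% test. It is a separate sample-size issue.

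**What to change.** Delete the ANOVA gate and the Tukey step. Name one primary test: the CKJ-minus-placebo difference in wheal size at week 12, adjusted for the baseline (screening) value, reported with its 95% CI and with sidedness stated. At the least, name the group-by-visit contrast from the model already planned. State that the efficacy conclusion rests on that between-arm contrast only.

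The cost is about two sentences in the statistical section, settled before unblinding. The data needed are already in the visit schedule, so there is no extra visit, measurement or participant burden.
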